##### Self-Esteem

Self-esteem will be measured with the Japanese version of the Rosenberg Self-esteem Scale, which consists of 10 items measured on a 4-point Likert scale. This scale is a 2-factor structure. The reliability and validity of the Japanese version of the Rosenberg Self-esteem Scale were verified in a previous study. Reliability of the Rosenberg Self-esteem Scale is very good with Cronbach *α*=.89 [33].

##### Resilience

We will use the Tachikawa Resilience Scale [34], which consists of 10 items measured on a 7-point Likert scale. This scale measures an individual’s resilience, or reactions to stressful life events. Higher scores reflect higher resilience. Reliability of the Tachikawa Resilience Scale is very good with Cronbach *α*=.82 [34].

##### ACT as Gatekeeper

We asked participants 2 months after the *t*_1_ survey about their behavior as gatekeepers for the last 2 months (see Multimedia Appendix 1 for questionnaire). We asked the frequency of the following: asking acquaintances (friends) about suicidal thoughts, distress, or depressed mood; listening to an acquaintance (friends); providing appropriate information; taking acquaintance (friends) to the right resource; and noticing suicide danger signs.

##### Demographic Characteristics

Demographic data such as sex, age, grade, school type, school location, living status, international student status, part-time job situation, whether one goes to school, online class status, state of emergency or preemergency measures for COVID-19, and experience in contact with people who have suicidal ideation will also be collected.

#### Process Evaluation

Since the number of sections each participant follows could influence the scores on the questionnaires, participants in the intervention group are asked to answer for the section they watched in the questionnaire survey after the intervention program.

For process evaluation, we use the Implementation Outcome Scales for Digital Mental Health (iOSDMH) [35]. We will use the 19 items of implementation outcomes for digital health interventions. This measurement is based on 3 important concepts: acceptability (*α*=.67), appropriateness (*α*=.78), and feasibility (*α*=.83). Adverse effects (ie, harms [*α*=.78]) of eHealth interventions, such as physical symptoms (eg, tired eyes, stiff shoulders), mental symptoms (eg, insomnia), and dangerous experiences (eg, bumping into people while looking at a smartphone), will be covered in 5 items.

#### Subgroup Analysis

##### Impact of COVID-19

The researchers collected data about fears of COVID-19 to capture the impact of COVID-19 on daily life using the Japanese version of the Fear of COVID-19 Scale (FCV-19S), as the target population was recruited during the pandemic. The scale, which consists of 7 items measured on a 5-point Likert scale, consists of 2 dimensions: emotional fear reactions and symptomatic expressions of fear. The higher the score, the stronger the fear of COVID-19. The validity of the Japanese-language version of FCV-19S was verified in a previous study. Reliability of FCV-19S is very good with Cronbach *α*=.87 [36].

##### Internet Use

To assess levels of internet addiction, we will use the Japanese version of the Compulsive Internet Use Scale (CIUS), which consists of 14 items measured on a 5-point Likert scale [37]. CIUS has 3 factors: excessive absorption, difficulty in setting priorities, and mood regulation. The higher the total score, the stronger the dependence on internet use. Reliability and validity of the CIUS were verified in a previous study. Reliability of CIUS is very good with Cronbach *α*=.93 [37].

### Sample Size Calculation

The sample size calculation is based on the difference between means of change in the primary outcome (self-efficacy as the gatekeeper) from baseline (preintervention) to postintervention (*t*_1_ survey) in both arms (complete case analyses). Based on previous studies on GKT, mean effect sizes of around *d*=0.5 are expected in per-protocol analyses for improving self-efficacy [12,22-25]. In order to detect such intervention effects in 2-tailed significance testing (*α*=.05) with a power of 80%, a sample size of 64 per group (total 128) participants is required. We assume the study dropout rate will be higher in web-based intervention and assessments compared to face-to-face research. The expected study dropout was about 60% (dropouts occur at random within each group), and this meant that 320 participants (160 per group) must be included in the study.

### Randomization and Blinding

After baseline assessment, participants will be randomly assigned to either group using the permuted block method with a random block size of 2, and they will be informed of their assigned group by the first author (KN). Randomization will be stratified by sex. The computer-generated allocation list was made by an independent researcher (YM). The enrollment is conducted by the first author (KN), and the intervention starts immediately. The means for blinding in this study are limited. An independent researcher (YM) who will not analyze data will download data from the GKT database. An independent research staff person will mask the group variable before analysis, and then researchers (KN) will analyze data that is blinded to the group variable.

### Statistical Analysis

The primary analysis for the GKSES score will be on a modified intention-to-treat principle, in which all available measurements are compared according to assigned groups. Baseline variables will be summarized by the groups using frequencies and proportions (for categorical variables) or mean and standard deviation (for continuous variables). The primary end points (difference of GKSES total score between presurvey and postsurvey) between the intervention group and the control group will be compared based on a *t* test. We will set the 2-sided significance level at 5%, and the 95% confidence interval of the average difference in differences of the scores will be estimated. Secondary end points will be compared similarly. As subgroup analysis for primary and secondary end points, we will stratify by highly dependent and lesser dependent groups for internet use, a group with high fear of COVID-19 and a group with low fear of COVID-19. To help interpretation, Cohen *d* and its 95% confidence intervals will be calculated at each assessment point; the values of 0.2, 0.5, and 0.8 are considered as small, medium, and large effects, respectively [38]. Statistical analysis will be performed using SPSS (version 27, IBM Corp) statistical software.

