**Methods:**

This study is a 2-arm, parallel, randomized controlled trial with a 1:1 (intervention: waiting list) allocation. Participants (n=320) will be recruited, and those who meet the inclusion criteria will be randomly allocated to the intervention or waiting list control group. An approximately 85-minute, 6-section, internet-based gatekeeper program for postsecondary students has been developed that includes videos to help participants acquire skills as gatekeepers. The intervention group will complete the program within 10 days. The primary outcome, self-efficacy as a gatekeeper, is measured using the Gatekeeper Self-Efficacy Scale at baseline, immediately after taking the program, and 2 months after the survey after completing the program follow-up. To compare the primary outcomes, a *t* test, where the significance level is 5% (2-sided), will be used to test the intervention effect on an intention-to-treat basis.

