## Methods

### Trial Design

Figure 1 shows the participant flow and study design. This study will be a 2-arm parallel-group nonblinded RCT with a GKT intervention group and a waitlist control group. Eligible participants are required to complete the baseline survey (*t*_0_) and are randomly allocated at a 1:1 ratio either to the intervention group or the control group. All surveys will be conducted via online questionnaires. Online follow-up surveys will be implemented about 10 days after the *t*_0_ survey (*t*_1_: immediately after the intervention), and at 2 months after the *t*_1_ survey (*t*_2_). After the 2-month follow-up, the GKT program will be provided to participants in the control group who wish to attend. This manuscript has been written according to the Standard Protocol Items: Recommendations for Interventional Trials (SPIRIT) guidelines [26].

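### The primary t test uses only t1 responders, about 128 of 320 by the plan's own figures, under three different labels; it is unbiased only if outcome-related non-response is absent or equal across arms

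*Protocol article*

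**What the plan says.** **Primary analysis.** The Statistical Analysis section of the protocol article applies a "modified intention-to-treat principle, in which all available measurements are compared according to assigned groups". The primary endpoint is the pre-to-post difference in GKSES, compared between arms by a t test.

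**Abstract.** The Methods paragraph says that a t test "will be used to test the intervention effect on an intention-to-treat basis", without the word modified.

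**Sample size.** The Sample Size Calculation section bases the size on the mean change from baseline to t1 and describes this as complete case. Effects of about d = 0.5 "are expected in per-protocol analyses for improving self-efficacy", and "with a power of 80%, a sample size of 64 per group (total 128) participants is required". On attrition it states: "The expected study dropout was about 60% (dropouts occur at random within each group" (the parenthesis closes there), and "this meant that 320 participants (160 per group) must be included in the study".

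**How t1 is collected.** Under Procedure, the intervention arm is told to answer t1 straight after the programme, which is to be taken within 10 days of the notice of allocation. The control arm answers 10 days after t0. Everyone completes the baseline survey before randomisation. Non-respondents get at least two reminders (Outcomes), and those who answer all three surveys enter a gift-card lottery (Procedure).

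**The concern.** The primary test is expected to leave out 60% of those randomised. Randomisation protects the comparison of 160 with 160, but not automatically the comparison of the students in each arm who choose to answer t1.

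The route to answering differs by arm. In the intervention arm, t1 comes at the end of a programme of about 85 minutes. In the control arm it is a questionnaire on a set day. Allocation is open and the outcome is self-rated confidence. The students who respond could therefore be selected differently in the two arms. Part of the observed difference would then reflect who answered, and the nominal 5% error rate would not hold.

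The three labels add to this. A reader of the abstract would expect everyone randomised to be in the comparison.

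**Working it through.** **1. The plan's own figures.** Inputs from the protocol: two-sided 5% level, 80% power, d = 0.5, 1:1 allocation, 60% dropout.
- The exact (noncentral t) power of a two-sample t test is 79.5% with 63 per group and 80.1% with 64, so 64 per group is right.
- 64 / (1 − 0.6) = 160 per group, 320 in all. This reproduces.
- Analysed: 128 / 320 = 40%. Not in the primary test: 320 − 128 = 192.

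The section does not say at which survey the 60% applies. It uses the figure to inflate a sample size for t1, so it is read as t1 here.

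**2. When responders-only analysis is biased.** Let m be the share missing in an arm and g the mean change in responders minus that in non-responders, in SD of change. The responder mean exceeds the full-arm mean by m × g, so

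bias = m_I × g_I − m_C × g_C.

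- If g = 0 in both arms, the bias is 0 whatever the dropout rates. Only power changes: 80% at 60/60 missing, 78% at 70/50 (48 v 80 analysed), 68% at 80/40 (32 v 96).
- If m and g are the same in both arms, the bias cancels.
- If g is equal but m differs, some bias remains. With g = 0.5 in both arms, 70/50 missing gives 0.7 × 0.5 − 0.5 × 0.5 = 0.10 SD and 8% rejection under the null; 80/40 gives 0.20 SD and 16%.

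**3. Selection on a trait related to change.** Assumptions, none of them in the protocol: 40% response in each arm, no true effect, and response when a normal trait correlated r with the GKSES change exceeds a threshold. The responder mean is shifted by r × φ(z)/0.4. With z = 0.253 and φ(z) = 0.386, the factor is 0.386/0.4 = 0.966.

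| r, intervention | r, control | Shift (SD) | Rejection, 64 v 64 |
|---|---|---|---|
| 0.3 | 0.3 | 0 | 5% |
| 0.3 | 0.2 | 0.1 × 0.966 = 0.10 | 8% |
| 0.1 | 0 | 0.10 | 8% |
| 0.2 | 0 | 0.19 | 19% |
| 0.3 | 0 | 0.29 | 37% |

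The planned effect, for scale, is 0.5 SD.

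**4. Selection on baseline confidence.** Suppose response in the intervention arm only depends on a trait correlated 0.3 with baseline GKSES, and assume a t0–t1 correlation of 0.5.
- Responders' baseline mean is 0.3 × 0.966 = 0.29 SD too high, and their expected change moves by (0.5 − 1) × 0.29 = −0.145, or about −0.15 SD.
- At that correlation the SD of change equals the SD of GKSES, since 2 × (1 − 0.5) = 1, so the scale is the same as in step 3.
- The change-score t test is biased against the programme and rejects a true null about 13% of the time.
- In simulation, a baseline-adjusted analysis of the same data has bias of about 0 and 5% rejection.

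**5. Limit of adjustment.** If the trait in step 3 predicts change but not baseline, the baseline-adjusted estimate in simulation carries the same 0.29 SD bias as the t test.

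**The case against.** **The plan does not hide its analysis set.** The Statistical Analysis section says modified and states that available measurements are compared by assigned group, which is compatible with sizing on complete cases. Only the abstract drops the qualifier. This stands: the label problem is a wording correction.

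**The stated assumption is close to what is needed.** Dropout at random within each group, read as unrelated to change, gives an unbiased contrast. This also stands. A reader might infer that arm-specific dropout passes straight into the treatment effect, or that the estimate is valid only if dropout is completely at random in both arms. The protocol supports neither. Unequal rates alone cost power, and equal selection cancels.

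**The direction is open.** A reader might infer that motivated students stay and so inflate the benefit. Step 4 shows that selection on baseline confidence pushes the other way.

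**Finishing the programme is not a condition of answering t1.** The survey goes to both arms, and the Process Evaluation section asks intervention participants which sections they watched, so partial viewers can respond. Reminders and the lottery may raise response. These points weaken the asymmetry but do not remove it.

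**A likelihood model is no cure for selection on an unmeasured trait.** This is correct (step 5). Missing-data sensitivity analyses may also sit in an analysis plan that is not shown, so their absence here is not the criticism. The point concerns the primary analysis that the protocol does fix.

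**Conclusion.** The point holds in a limited form. The protocol fixes a responders-only t test on change as its primary analysis, expects it to cover about 128 of 320 randomised students, and gives that one analysis three labels. The sample size arithmetic is correct.

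Whether the result is biased depends on outcome-related non-response that differs by arm. The collection of t1 makes this plausible, and the planned test can neither check nor adjust for it. On the assumed values the consequence runs from nothing (equal selection), through about 0.10 SD and 8% rejection (0.3 v 0.2), to 0.29 SD and 37% (0.3 in the intervention arm only). Baseline-driven selection gives about −0.15 SD. The correlations and the arm-specific response rates are assumptions, and 60% is a planning allowance. The protocol does not support taking the 37% case as the expected one.

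The case for change is that baseline data will exist for every randomised participant, and the planned test uses only the responders' own baseline GKSES.

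**What to change.** - Make the primary analysis a baseline-adjusted, likelihood-based repeated-measures model on all randomised participants (GKSES at t0, t1 and t2; arm-by-time; sex), with the t1 contrast primary. Multiple imputation using the baseline variables (GKSES, K6, CIUS, FCV-19S, demographics) is an alternative. Either can also use t2 data from students who missed t1.
- State that this removes bias from dropout explained by measured data only. Support it with a delta-adjusted sensitivity analysis in which the shift can differ by arm.
- Report t1 response by arm.
- Keep the t test as a supportive analysis, labelled complete case by assigned group.
- Align the wording in the abstract, the Sample Size Calculation section and the Statistical Analysis section with the analysis set actually used.

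Cost: no new data, a few more model runs, and slightly more complex analysis and reporting. The change should be fixed before the group variable is unmasked.

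### The primary t test on GKSES change is valid but inefficient: it uses neither baseline GKSES as a covariate nor the sex stratification factor

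*Protocol article*

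**What the plan says.** All references are to the protocol article. Statistical Analysis fixes the primary comparison: "The primary end points (difference of GKSES total score between presurvey and postsurvey) between the intervention group and the control group will be compared" by a t test. For the effect estimate, "the 95% confidence interval of the average difference in differences of the scores will be estimated". No covariate is named, and secondary end points are to be handled in the same way. The Abstract also names a t test for the primary outcome.

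Randomization and Blinding states: "Randomization will be stratified by sex". Allocation is made "using the permuted block method with a random block size of 2". Trial Design and Procedure place the baseline survey before allocation, so every randomised participant has a baseline GKSES score.

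Sample Size Calculation uses the same quantity as the test: "The sample size calculation is based on the difference between means of change in the primary outcome", from baseline to t1, in complete cases. It takes d=0.5, two-sided alpha 0.05 and 80% power, giving 64 per group. With about 60% dropout, 320 are to be randomised.

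**The concern.** The plan holds two pieces of pre-randomisation information that could sharpen the comparison, and the stated analysis uses one of them crudely and the other not at all. Subtracting baseline is the same as adjusting for it with the slope forced to 1. When the true slope is below 1, this adds noise and moves the estimate in the direction opposite to any baseline imbalance.

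The confidence interval for the primary result would then be wider than the data require, and so would the interval for each secondary outcome with a baseline measure. It matters more than usual here because the plan expects only 128 of 320 participants to be analysed. The balance created at randomisation is not assured among those who remain.

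**Working it through.** **1. The plan's own figure.** Inputs from Sample Size Calculation: d=0.5, alpha 0.05 two-sided, power 80%, dropout 60%. The exact two-sample t-test solution is 63.77, so 64 per arm, with power 0.801. Inflation: 128/(1-0.6) = 320, or 64/(1-0.6) = 160 per arm. Both stated figures reproduce.

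**2. Variance of the two analyses.** Assume equal pre and post variances s² and correlation r between baseline and t1. Neither is given in the article; r from 0.3 to 0.9 is shown.
- Per-person variance of change: 2s²(1-r)
- Per-person residual variance after adjusting for baseline: s²(1-r²)
- Ratio: (1-r²)/(2(1-r)) = (1+r)/2, which is below 1 for every r below 1

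**3. Power at 64 per arm.** With d=0.5 on the change-score SD, as the plan applies it, the equivalent d under covariance analysis is 0.5/√((1+r)/2). The interval width relative to the t test is √((1+r)/2).

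| r | Variance ratio | Equivalent d | Power, t test on change | Power, covariance analysis | CI narrower by | n per arm for 80% |
|---|---|---|---|---|---|---|
| 0.3 | 0.65 | 0.620 | 80% | 94% | 19% | 42 |
| 0.5 | 0.75 | 0.577 | 80% | 90% | 13% | 48 |
| 0.7 | 0.85 | 0.542 | 80% | 86% | 8% | 55 |
| 0.9 | 0.95 | 0.513 | 80% | 82% | 3% | 61 |

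The last column is 64 × (1+r)/2, rounded up.

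**4. Simulation check.** There were 4,000 runs per setting with 64 per arm, sex balanced across arms, and a sex effect of 0.3 SD at both baseline and t1. The covariance model included baseline and sex. Power, change score against covariance analysis, was 81% and 94% at r=0.3, 80% and 89% at r=0.5, and 82% and 87% at r=0.7. Type I error was 0.052 to 0.058 for the change score and 0.046 to 0.054 for covariance analysis. Both estimates were unbiased on average.

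**5. Effect of a chance baseline imbalance.** At 64 per arm the standard error of the baseline difference is √(2/64) = 0.177 SD, so a 1.96-SE imbalance is 0.35 SD. Given that imbalance, the change-score estimate is off by -(1-r) × 0.35 SD. The target effect on the raw-score scale is 0.5 × √(2(1-r)) SD.

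| r | Conditional error (SD) | Target effect (SD) | Error / target |
|---|---|---|---|
| 0.3 | -0.24 | 0.59 | 41% |
| 0.5 | -0.17 | 0.50 | 35% |
| 0.7 | -0.10 | 0.39 | 27% |
| 0.9 | -0.03 | 0.22 | 15% |

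The sign is opposite to the imbalance, so this is over-correction. Over repeated randomisation it averages to zero.

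**The case against.** The strongest reply is that nothing here is wrong. The trial is sized on the difference in mean change and tests that same difference. The sample size reproduces, the type I error is near 5%, and the estimate is unbiased over randomisation. The planned 80% power needs no adjustment. All of this stands, and it limits the point to efficiency.

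Four stronger readings are tempting, and the document does not support them:
- *Baseline imbalance goes uncorrected.* It does not. The change score subtracts baseline, and the fault is over-correction by a fixed slope of 1.
- *Leaving out sex invalidates the test or its standard error.* A stable sex effect cancels in the change score. Only a sex effect on change itself would matter, and the omission then makes the test at most mildly conservative.
- *The trial is underpowered.* Sample Size Calculation draws its effect size from earlier studies ("mean effect sizes of around *d*=0.5 are expected in per-protocol analyses for improving self-efficacy") and does not name the SD behind it. If that SD were of the raw score and r were 0.3, the t test would have about 66% power and covariance analysis 84%. This needs both a reading of d other than the change-score one on which the section bases its calculation and an r at the bottom of the assumed range. On the same reading the t test has about 80% power at r=0.5 and 95% at r=0.7.
- *Heavy attrition makes the estimate biased.* The plan assumes dropout at random within each group. If dropout were differential, that would be a missing-data problem, which baseline and sex adjustment would solve only in part. Attrition is a reason not to rely on the balance achieved at randomisation, and no more than that.

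A further fair objection is that the change is not free, since it comes after recruitment. That also stands and is taken up in the fix.

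**Conclusion.** The point holds as an efficiency weakness that should be put right. The article states its primary method outright, so this is a choice made and not a detail left to a fuller plan. Analysis of covariance would have 65% to 95% of the change-score variance for r from 0.3 to 0.9, taking power from 80% to between 94% and 82% if 128 participants complete. It would also remove the conditional error from a chance baseline imbalance.

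The direction of the gain is certain for any r below 1 under equal pre and post variances. Its size is not, because r is not in the document, and near r=0.9 the gain is small. Adding sex is the lesser part of the point: it aligns the analysis with the design and guards against imbalance among completers, but no material gain is claimed for it.

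**What to change.** Make the primary model a linear model of t1 GKSES on arm, baseline GKSES and sex, and report the adjusted difference between arms with its 95% confidence interval. Use the same form for each secondary outcome that has a baseline measure. Behaviour as gatekeeper has none and cannot be adjusted this way. Keep the t test on change as a sensitivity analysis, and keep n=320, because r is unknown and the gain should not be spent on a smaller sample.

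The cost is small but not zero. No new data are needed, and the model can be fitted in the software already named. The Results section puts recruitment in August and September 2021 and data collection through December 2021, so the primary analysis would be changed while the trial is running. The change must be dated before the group variable is unmasked and recorded by the route in Research Ethics and Approval: ethics committee approval and a revised registry entry.

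### Subgroup effects are to be examined within high and low strata of two graded scales, with no contrast between strata, so the stated method cannot show whether the effect differs

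*Protocol article*

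**What the plan says.** The Statistical Analysis section of the protocol article compares the pre-to-post change in GKSES between arms by a t test at a two-sided 5% level, with a 95% confidence interval for the difference in change. Secondary end points are to be handled in the same way. For the subgroup analysis of all these end points the text reads "we will stratify by highly dependent and lesser dependent groups for internet use", and it adds high and low groups on fear of COVID-19.

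Both factors are graded baseline scores. Of the CIUS (14 items, 5-point), the Internet Use section says "The higher the total score, the stronger the dependence on internet use". Of the FCV-19S (7 items, 5-point), the Impact of COVID-19 section says "The higher the score, the stronger the fear of COVID-19". The article names no interaction term, no contrast between strata and no model that uses either score as a continuous variable. It does not call the subgroup analyses exploratory.

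**The concern.** A subgroup analysis asks whether the effect in one group differs from the effect in another. Two separate comparisons, one per stratum, each ask whether there is an effect in that stratum. Neither answers the question. One stratum can be significant and the other not when the true effects are identical, simply because each holds only part of the sample. The reverse also happens: both can be significant, or neither, when the effects do differ.

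At stake is a statement such as: the programme works for students with low internet dependence but not for those with high dependence. For a programme meant for wide online distribution, that statement could affect who is offered it. Cutting a graded score into two levels also discards the information within each level.

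**Working it through.** **Inputs**

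- Two-sided significance level 5% (Statistical Analysis).
- Power and completers: "with a power of 80%, a sample size of 64 per group (total 128) participants is required" (Sample Size Calculation).
- Effect: "mean effect sizes of around" d = 0.5, described there as a per-protocol expectation.
- Allocation 1:1 (Trial Design).
- Dropout about 60%, so 320 randomised, 160 per arm (Sample Size Calculation).
- Stratum shares: not stated. **Assumption:** 50/50, with 30/70 and 20/80 as the range.

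**The protocol's own figure.** For d = 0.5, 5% two-sided and 80% power, the noncentral t distribution gives 63.77, so 64 per group. Then 128 / (1 − 0.60) = 320. The stated figures reproduce.

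**Power within one stratum.** A 50/50 split of 64 completers per arm leaves n = 32 per arm per stratum. The noncentrality is d × √(n/2) = 0.5 × √16 = 2.0 on 62 degrees of freedom, and power is 0.504.

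**Chance that exactly one stratum is significant when the true effect is the same in both.** With stratum powers p1 and p2, this is p1(1 − p2) + p2(1 − p1).

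- 50/50 (32 and 32 per arm): 2 × 0.504 × 0.496 = 0.50.
- 30/70 (19 and 45 per arm): 0.323 × 0.350 + 0.650 × 0.677 = 0.553.
- 20/80 (13 and 51 per arm): 0.232 × 0.294 + 0.706 × 0.768 = 0.610.

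**Sensitivity to effect and retention, 50/50 split**

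| True d in both strata | 64 per arm | 160 per arm (no dropout) |
|---|---|---|
| 0 | 9.5% | 9.5% |
| 0.2 | 22% | 37% |
| 0.3 | 34% | 50% |
| 0.5 | 50% | 21% |
| 0.8 | 21% | 0.2% |

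For equal strata the expression is 2p(1 − p), which peaks at 0.50 when p = 0.5. The planning values fall almost exactly on that peak. Full retention lowers the figure at d = 0.5 but raises it at d = 0.2 and 0.3.

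**Both factors together.** In a simulation of 5,000 trials per scenario (median splits, d = 0.5, no true interaction, the two scores uncorrelated or correlated 0.3), at least one of the two factors showed the discordant pattern on the primary outcome in about 67% of trials with 64 per arm. With 160 per arm it was about 31%.

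**Interaction test in the same simulation.** The false-positive rate for one factor was 4.3 to 4.7% with 64 per arm and 5.0% with 160 per arm. This is what a valid 5% test should give.

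**Power of the interaction test.** With 32 per arm in each of two strata and SD 1, the standard error of the difference between stratum effects is √(4/32) = 0.354. For a true difference of 0.5, power is Φ(0.5/0.354 − 1.96) = Φ(−0.55) = 0.29. For 0.25 it is 0.11. With 160 per arm and a difference of 0.5 it is 0.61.

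**The case against.** A reader might infer that the protocol plans to declare moderation whenever one stratum is significant and the other is not. The text does not support that. It never speaks of moderation and gives no decision rule. It also commits to 95% confidence intervals for the difference in change and to Cohen d with intervals as an aid to interpretation. If these are carried into the strata, a reading by significance alone becomes less likely. The discordance figures therefore describe what would follow from one way of reading the results, not a stated plan.

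A reader might also take 50% as a fixed rate. It is the maximum for equal strata and rests on the assumed split, the planned effect and the expected dropout, so it must be read with its range.

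The article is condensed, and cut-offs or an exploratory label may sit in a fuller document. Their absence is not counted here. Stratum estimates are also compatible with an added interaction test. What remains is that the article does state a subgroup method, and that method does not address the question a subgroup analysis exists to answer.

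Finally, neither the Objectives nor the hypotheses in Strengths of the Study mention subgroups. That limits the weight of the point but does not remove it, since the analysis is specified for every primary and secondary end point.

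**Conclusion.** The point holds as a criticism of the subgroup method. Within-stratum comparisons of two dichotomised scales, with no contrast between strata, cannot show whether the effect differs. If significance is compared across strata, the chance of a misleading pattern per factor is about 50% at the planning values with a 50/50 split. With that split and 64 per arm it ranges from about 10% at d = 0 through 21 to 34% at d = 0.2, 0.3 or 0.8. Unequal splits raise it to 55 to 61% at d = 0.5, and full retention lowers it to 21% at that effect. An interaction test holds it at about 5%.

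The planned d = 0.5 is a per-protocol figure, whereas the analysis is by assigned group, so a smaller effect is plausible. At d = 0.3 the figure is 34% with 64 per arm and 50% with 160.

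One might infer that the trial's main result is in doubt. It is not: the primary comparison and the sample size are untouched, and only subgroup statements are affected.

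**What to change.** For each end point, fit a linear model of the change score with arm, the continuous baseline CIUS score and their product, and a second model with FCV-19S in place of CIUS. ACT has no baseline measurement in Table 2, so the two-month value would be the outcome there. Report each interaction with its 95% CI, base any subgroup claim on it alone and label it exploratory. Show high and low stratum estimates with 95% CIs as description, without within-stratum p-values.

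Both scales are already collected at baseline, so the cost is wording and two models per end point. Three downsides should be stated:

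- The product term assumes that the effect changes roughly linearly with the score.
- Power is low: about 29% for a between-stratum difference of d = 0.5 with 50/50 strata and 64 per arm. That figure is for the two-level form; it was not computed for the continuous score. The result is an estimate, not a confirmatory test, and a non-significant interaction does not show that effects are equal.
- Nine end points by two factors still make 18 interaction tests, with 18 × 0.05 = 0.9 false positives expected if no interaction exists. This is a further reason for the exploratory label.
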